##### For caregivers

*Experience of Caregiving Inventory* (ECI) [57]. The ECI is composed of 66-items and is designed to measure how a person caring for someone with a serious mental illness appraises his/her experience. It is composed of ten subscales, eight of which measure negative aspects of caregiving (difficult behaviors, negative symptoms, stigma, problems with services, effects on family, need to backup, dependency and loss) and two measure positive aspects (rewarding personal experiences and good aspects of relationship with the patient), which can be grouped into two subscales: the ECI-negative and the ECI-positive. Responses are on a 5-point Likert scale (ranging from 0 = “never” to 4 = “nearly always”). Higher scores indicate a more positive or negative appraisal of the caregiving experience. The ten scales showed satisfactory reliability with Cronbach’s α ranging from 0.74 to 0.91. The internal reliability coefficients of the caregivers were 0.81 for the ECI-positive and 0.92 for the ECI-negative.

*EQ-5D-5 L* [48].

*iMTA questionnaire for Costs associated with Psychiatric Illness, Parent-Form* (TiC-P Children). The Dutch version of the TiC-P Children has been used to measure medical and non-medical costs in children with mental health disorders. The questionnaire was obtained upon permission from the original authors and was translated from Dutch into Spanish by our research group.

#### Qualitative assessment

In order to perform the economic evaluation, all relevant costs due to healthcare utilization (number of visits to ED specialists, number of visits to the emergency department, medication consumption and its costs) as well as other costs related to the implementation of the online intervention with the TCApp for both clinicians responsible for the online treatment and technicians (amount of extra working hours) will be evaluated through a telephone interview with each stakeholder.

### Sample size calculation

The a priori sample size calculation was based on results from previous studies that implemented Internet-based programs in the treatment of EDs [58–60]. A small between-group effect size (Cohen’ s d = 0.40) is expected. The calculation was conducted by the software program G*POWER. The primary analysis will concern the hypothesis that the average level of eating pathology at post-intervention in the control group, based on the EDE-Q scores, will be higher than the average levels of eating pathology in the experimental group. Assuming an alpha of 0.05 and a power of 0.80 (β − 1) in an independent samples one-way t-test study, a minimum of 100 participants would be required per study arm. Allowing for a dropout rate of 25% of study participants from baseline, a total of 250 participants need to be recruited.

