## Methods

### Design

We will follow a mixed-methods approach, combining quantitative and qualitative methods, through a multi-centre RCT with two parallel groups (an intensive intervention group with TAU and TCApp and a TAU control condition) with a 1:1 allocation.

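### The 250 recruits allow for 20% dropout, not the stated 25%, and the sidedness of the test behind the 100 per arm is left unclear

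*Protocol article*

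**What the plan says.** All the figures stand in one paragraph of the protocol article, Methods, Sample size calculation.

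- Effect: "A small between-group effect size (Cohen’ s d = 0.40) is expected".
- Error rates: "Assuming an alpha of 0.05 and a power of 0.80".
- Test and requirement: "in an independent samples one-way t-test study, a minimum of 100 participants would be required per study arm".
- Recruitment: "Allowing for a dropout rate of 25% of study participants from baseline, a total of 250 participants need to be recruited".

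The hypothesis is directional: mean EDE-Q pathology after the intervention in the control group "will be higher than the average levels of eating pathology in the experimental group". The paragraph does not call the test one- or two-sided. The Design section gives two parallel groups "with a 1:1 allocation".

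The target of 250 is repeated in the abstract, the Background, the Sample section and the Statistical analysis section, in some places as an approximate number. The Statistical analysis section announces both an intent-to-treat analysis of all 250 and a completers analysis, and says that the treatment effect on the main outcome will rest on completers only.

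**The concern.** Two things in the paragraph do not fit together.

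First, the dropout rate is defined on the patients present at baseline, so the number left is the number recruited times 0.75. From 250 that falls below the protocol's own minimum of 100 per arm.

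Second, *one-way* is not a standard description of a t-test. Beside a directional hypothesis it may be taken as one-tailed, but 100 per arm is not the one-tailed requirement.

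At stake is whether the stated sample size, dropout allowance and power can all be true at once. Because the main treatment effect is to be estimated in completers, dropout reduces that analysis directly.

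**Working it through.** **Inputs** (Sample size calculation and Design): d = 0.40, alpha 0.05, power 0.80, allocation 1:1, 100 evaluable per arm, 25% dropout from baseline, 250 recruited.

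**1. Reproducing the 100 per arm.** The normal approximation is n per arm = 2(z_alpha + z_power)² / d².

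- Two-sided: 2(1.960 + 0.842)² / 0.16 = 98.1, so 99. The exact noncentral t calculation gives 99.08, so 100. Power at 100 per arm is 0.804.
- One-sided: 2(1.645 + 0.842)² / 0.16 = 77.3, so 78. The exact calculation gives 77.97, so 78. Power at 78 per arm is 0.800; at 100 per arm it would be 0.880.
- One-way analysis of variance with two groups, f = d/2 = 0.20: total 198.2, so 100 per arm. This test is equivalent to the two-sided t-test.

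The stated 100 is therefore the two-sided figure.

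**2. Reproducing the 250.**

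- 200 x (1 + 0.25) = 250. This matches the stated target.
- 200 / (1 − 0.25) = 266.7, so 267, or 268 (134 per arm) with equal arms. This is what a 25% loss from baseline requires.
- Starting from 99 per arm, 198 / 0.75 = 264, which is still not 250.
- Starting from the one-sided 78 per arm, 156 / 0.75 = 208.

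**3. What 250 leaves.** 250 x 0.75 = 187.5, or 93.75 per arm. The dropout rate at which 250 still leaves 200 is 1 − 200/250 = 20%.

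**4. Power at 93.75 per arm.** The noncentrality is d x √(n/2) = 0.40 x √46.875 = 2.739.

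| Test at alpha 0.05 | Normal approximation | Exact t | d detectable with 80% power (exact t) |
|---|---|---|---|
| Two-sided | 0.782 | 0.778 | 0.411 |
| One-sided | 0.863 | 0.861 | 0.365 |

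**5. Setting the readings side by side.**

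| Reading | Per arm needed | Recruits needed at 25% dropout | Power of 250 recruits at 25% dropout |
|---|---|---|---|
| As stated | 100 | 250 | 0.80 |
| Two-sided | 100 | 267–268 | 0.78 |
| One-sided | 78 | 208 | 0.86 |

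The two-sided row agrees with the protocol on the 100 but not on the 250 or the power. The one-sided row agrees on neither the 100 nor the 250.

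**The case against.** The strongest defence is that the consequence is slight. Under the two-sided reading, power falls from 0.804 to 0.778 and the detectable effect rises from 0.40 to 0.41. The target is also called approximate in places. The plan further includes an intent-to-treat analysis of all 250, a mixed model over time and attempts to collect data from patients who drop out, so 94 per arm is not the only number that may be analysed. All of this stands as to size. It does not repair the arithmetic, because the dropout rate is explicitly counted from baseline and the completers rule carries the loss into the main treatment effect.

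A second defence concerns the label. Read as a two-group one-way comparison, *one-way* agrees exactly with 100 per arm, and a directional hypothesis does not by itself fix the sidedness of the test. This also stands: the wording is unclear, but it is not proof that text and figure describe different tests.

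Three stronger readings are tempting, and the document does not support them.

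- A reader might infer that 80% power is missed however the test is read. It is missed only under the two-sided reading; under the one-sided reading power is about 86%.
- A reader might infer that the trial will test one-sided at 0.05 and so double the false-positive risk in favour of the app. The Statistical analysis section announces no one-sided test, so this is hypothetical.
- A reader might infer that adjusting for baseline EDE-Q makes up the lost power. Any gain depends on the correlation between baseline and post-treatment scores, which the document does not give.

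**Conclusion.** The dropout inflation is wrong as written. The protocol's 250 corresponds to 20% dropout; at the stated 25% it leaves about 94 per arm, 6 short of the stated minimum. Under the two-sided test that reproduces 100 per arm, this costs a little over two percentage points of power (0.778 against 0.804). The sidedness is ambiguous, and neither reading makes the 100, the 25%, the 250 and the 80% agree.

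This is a minor correction of a stated figure and no threat to the trial's conclusion. The power figures assume d = 0.40, an unadjusted t-test and equal loss in the two arms. Loss in the app arm could be larger, because completers there must also reach 70% of the agreed app use, but the document gives no rate for this and no size can be put on it here.

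**What to change.** In the Sample size calculation section:

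1. Replace *one-way* with *two-sided* and state alpha as two-sided 0.05. This is the reading that reproduces 100 per arm.
2. Correct the dropout sentence in one of two ways. Either state that 250 recruits keep 100 per arm at up to 20% dropout, or keep the 25% and state that it leaves about 94 per arm, with about 78% power for d = 0.40 (80% for d = 0.41).

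If both the 25% allowance and the 100 per arm are to be kept, the target becomes 267, or 268 with equal arms, and every place that repeats 250 must change with it.

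Restating costs a few words and figures. The only downside is a slightly less favourable stated power or dropout allowance.

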### Data management

All data related to the trial, including clinician’s paper notes of the diagnostic interviews (K-SADS, SCID), self-report questionnaires, informed consent forms, and audio recordings of the telephone interviews, will be securely stored in the workplace of our research group located in the UOC. Only authorised researchers directly involved in the study will have access to this information. According to the UOC’s approval report, all obtained data will be kept for a minimum of 5 years. After obtaining the signed informed consent from participants, a unique code will be allocated to each one of them. The file that links participants to their codes and the databases will be also securely stored on a secure server, password-accessible only to the research team.

### Statistical analysis

Both intent-to-treat and completers analyses will be carried out. Intent-to-treat analysis will include every participant who will be randomly allocated to one of the study conditions, that is to say, 250 patients. Whenever possible, we will try to collect follow-up data from participants who have dropped out, in order to keep our dataset as complete as possible. Baseline differences between completers and dropouts will be analysed (Pearson’s chi-square test Student’s t test) using data from the clinical interviews and the baseline questionnaires and possible reasons for dropout will be examined through interviews with the ED specialists (T1, T2).

A participant will be considered a completer if he/she has completed the initial clinical interview as well as T0 and T1 evaluations. For participants from experimental group, to be considered completers they will have to have used the TCApp at least 70% of the time that was initially agreed upon before the start of the experiment (at least once a day during a period of 12 weeks). Only data from completers will be used to determine the treatment effect on the main outcome variable.

All analyses will be carried out using SPSS (Statistical Package for the Social Sciences). First, we will examine the data using descriptive statistics. Between-group analysis will be conducted using Pearson’s chi-square test or Fisher’s exact test for categorical data and Student’s t test or the Mann-Whitney U test for continuous variables, depending on the normality of the distribution. The normality of the distribution of the variable will be assessed using the Kolmogorov-Smirnov test. The effect of the intervention in terms of reduction in the primary and secondary outcome measures over time will be computed by using a mixed model linear regression analysis with time, experimental condition and their interaction as independent variables. Since there may be some heterogeneity in the implementation of the intensive online intervention across the different participating institutions, between-centre heterogeneity will be explored in subgroup analyses.

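### The main-outcome effect is assigned to completers only, with an app-use condition in one arm, so as written it is not a randomised comparison and conflicts with the promised ITT analysis

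*Protocol article*

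**What the plan says.** All the relevant rules stand in the protocol article under Statistical analysis. The section opens with "Both intent-to-treat and completers analyses will be carried out". It defines the first of these: "Intent-to-treat analysis will include every participant who will be randomly allocated to one of the study conditions, that is to say, 250 patients".

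It then defines a completer. For everyone: "A participant will be considered a completer if he/she has completed the initial clinical interview as well as T0 and T1 evaluations". For one arm there is a further condition: "For participants from experimental group, to be considered completers they will have to have used the TCApp at least 70% of the time". The agreed use is given as "at least once a day during a period of 12 weeks". The next sentence assigns the main result to this set: "Only data from completers will be used to determine the treatment effect on the main outcome variable".

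The same section later plans a mixed linear model for the primary and secondary outcomes and names no analysis set for it. Under Sample size calculation, the primary question is set at the post-intervention assessment (T1): "The primary analysis will concern the hypothesis that the average level of eating pathology at post-intervention in the control group, based on the EDE-Q scores".

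**The concern.** A patient becomes a completer, or fails to, after randomisation, and the test differs by arm. An experimental patient who attends T1 but used the app on half the days has a measured EDE-Q score that is set aside. A control patient who is just as disengaged from treatment, but attends T1, is kept. Controls cannot be filtered in the same way, because they have no access to the app until after T2.

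The comparison is therefore a selected arm against an arm selected only on attendance. If the patients who keep up daily use would have done better or worse anyway, that difference enters the treatment effect. Even an inert app could then appear to work, or a useful one could appear not to. The planned baseline comparison of completers and dropouts would describe such selection but would not correct the estimate. The Economic evaluation section also draws on the EDE-Q effect, so the problem could carry over there.

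**Working it through.** **Inputs from the article.** Alpha 0.05, power 0.80, d = 0.40, 100 per arm, 25% dropout, 250 in total, 1:1 allocation, a 12-week period and a 70% use threshold.

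**Inputs the article does not give (assumed, with a range).** The share *a* of retained experimental patients who meet the 70% rule, and the correlation *ρ* between app use and a better T1 EDE-Q score irrespective of treatment.

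**1. The plan's own figure.** A two-sided t-test at d = 0.40, alpha 0.05 and power 0.80 needs 99.08 per arm, so 100. This reproduces the stated figure. A one-sided test would need 78.

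**2. The usage rule.** 12 weeks × 7 = 84 days, and 0.70 × 84 = 58.8, so about 59 days of use.

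**3. Numbers analysed.** 125 per arm × 0.75 = 93.75, about 94 per arm after dropout. If the usage rule removes patients over and above the dropout, the experimental arm falls to 93.75 × *a*. At *a* = 0.6 that is 56.25, so about 56 against 94.

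**4. Bias with no true effect.** Treat use and outcome as bivariate normal with SD 1 and keep the top share *a* of users. With z = Φ⁻¹(1 − *a*), bias = *ρ* × φ(z)/*a*. At *a* = 0.6, φ(z)/*a* = 0.644, which gives 0.2 × 0.644 = 0.129 and 0.3 × 0.644 = 0.193. Against the planned effect these are 0.129/0.40 = 32% and 0.193/0.40 = 48%.

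**5. False-positive rate.** With m = φ(z)/*a*, the variance in the selected arm is 1 − *ρ*² × m(m − z). The standard error is √(variance/n_exp + 1/n_ctrl), and the two-sided rejection rate is Φ(−1.96 + bias/SE) + Φ(−1.96 − bias/SE). For *a* = 0.6 and *ρ* = 0.2, the variance is 1 − 0.04 × 0.644 × (0.644 + 0.253) = 0.977, and SE = √(0.977/56.25 + 1/93.75) = 0.167. The rejection rate is 0.120.

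| Share meeting rule | ρ | Bias (SD) | Two-sided error |
|---|---|---|---|
| 0.9 | 0.1 | 0.02 | 0.05 |
| 0.8 | 0.2 | 0.07 | 0.07 |
| 0.7 | 0.3 | 0.15 | 0.16 |
| 0.6 | 0.2 | 0.13 | 0.12 |
| 0.6 | 0.3 | 0.19 | 0.21 |
| 0.5 | 0.3 | 0.24 | 0.28 |

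A negative *ρ* gives a bias of the same size against the TCApp. With *ρ* = 0 there is none.

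**6. Power at d = 0.40, if the rule removes patients beyond the 25%.** 0.78 with 94 per arm (*a* = 1), 0.73 at *a* = 0.8, 0.65 at *a* = 0.6 (56 against 94), and 0.60 at *a* = 0.5. The step from 0.80 to 0.78 comes from how dropout was added (200 × 1.25 = 250, which leaves 94 per arm after 25% loss). Only the fall below 0.78 belongs to this point.

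**The case against.** The strongest reply is that ITT has not been abandoned. The section promises it, defines it on all 250 patients, seeks follow-up data from those who drop out, and describes the mixed model without restricting it to completers. The restricting sentence may have been meant to describe the completers analysis alone. A reader might infer that the plan has settled on completers and given up ITT, and the text does not support that. What does stand is that the sentence, read literally, gives the main-outcome effect to completers and nothing else withdraws it. The section contradicts itself at best.

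A reader might also infer that the bias is known to favour the TCApp. The article reports no link between use and outcome. Its use rule allows for contact with the therapist as needed, so patients who are more unwell might use the app more and those who improve early might stop. The direction is plausible, not shown.

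A third inference is that the 25% dropout allowance leaves out patients who fail the usage rule. The section contrasts only completers and dropouts, so such patients may already be counted within the 25%. In that case the further fall in power would count them twice.

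Finally, the illustration concerns a raw T1 difference, as in the sample size calculation. The Background section words the hypotheses as change scores, and the planned model has a time-by-condition term. If use is also related to baseline severity, part of the selection cancels in a change score, so the error rates above need not carry over to the mixed model.

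**Conclusion.** The plan is wrong as written. It names two analysis sets and then assigns the main-outcome effect to the one that filters a single arm on behaviour after randomisation. Loss of the randomised comparison follows from the definition and needs no assumption about direction.

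The size cannot be derived from the article. For a raw T1 comparison with 25% dropout and no true effect, it runs from negligible (about 0.02 SD, error about 5%, at 90% adherence and correlation 0.1) to serious (0.13 to 0.19 SD, error about 12 to 21%, at 60% adherence and correlations of 0.2 to 0.3). The sign reverses if heavier use goes with worse outcome. The loss of power from about 0.78 to about 0.65 at 60% adherence holds only if the 25% allowance does not already include patients who fail the usage rule.

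**What to change.** Delete the sentence that restricts the main-outcome effect to completers. State instead that the primary effect on the EDE-Q at T1 is estimated in all randomised patients in the arm to which they were allocated, with every available T0, T1 and T2 score in the planned mixed model, whatever the TCApp use. Keep the completers analysis, labelled as a sensitivity analysis. If the effect among those who use the app is of interest, a complier-average analysis is an option. It brings its own assumptions and is not needed to resolve this point.

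The cost is a change of wording. T1 is already scheduled for everyone, so no new assessment is required. Follow-up of dropouts is promised only where possible, so some T1 scores will still be missing. Two-sided power at d = 0.40 would be about 0.88 if all 125 per arm had T1 data, and about 0.78 with 94 per arm. The downside for the sponsor is that the estimate may be less favourable than one from completers.

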The purpose of this trial is to conduct a multicentre, randomized controlled trial with 250 patients diagnosed with an ED. In this experiment, the patients from the experimental group will test a mHealth application (TCApp developed by HealthApp) and then, a clinical efficacy analysis and economic evaluations will be performed. To do this, we have set the following three specific objectives:To evaluate the clinical efficacy of an intensive intervention that includes both standard face-to-face Cognitive Behavioural Treatment (CBT) (treatment as usual, TAU) plus mHealth intervention using the TCApp, versus the TAU alone.To carry out an economic evaluation of the new mHealth intervention and identify factors that promote or hinder the implementation of the TCApp in mental health settings in Spain.To analyse the adoption processes of this type of applications by patients and health professionals and identify the determinants of mHealth adoption.

The implementation of the intensive intervention program (TAU + TCApp) would result in a more significant improvement of the ED symptoms compared to the TAU control group. More specifically:The application of the intensive mHealth intervention would lead to significantly greater change scores (difference between T0 and T1, which will be also maintained at follow-up, T2) in the primary outcome variable of ED psychopathology, compared to the control group.The mHealth intervention would lead to significantly greater change scores (difference between T0 and T1, which will be also maintained at follow-up, T2) in patients’ secondary outcome variables: a) depression symptoms, b) anxiety symptoms, c) readiness to recover, d) suicidal risk, and e) quality of life, compared to the control group.Similarly, intensive intervention would result in greater change scores (difference between T0 and T1, which will be also maintained at follow-up, T2) in caregivers’ variables: a) quality of life and b) caregiver burden.

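### The trial is sized for the T1 difference in mean EDE-Q, but the planned mixed model expresses the effect as a time-by-condition interaction that is not tied to a T1 contrast

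*Protocol article*

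**What the plan says.** The Sample size calculation section fixes the target: "The primary analysis will concern the hypothesis that the average level of eating pathology at post-intervention in the control group" exceeds that in the experimental group, measured by the EDE-Q. It assumes "A small between-group effect size (Cohen’ s d = 0.40) is expected", an alpha of 0.05 and power of 0.80, "in an independent samples one-way t-test study". The result is 100 per arm, raised to 250 in total for 25% dropout.

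The hypotheses at the end of the Background are worded as change: "significantly greater change scores (difference between T0 and T1, which will be also maintained at follow-up, T2) in the primary outcome variable".

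The Statistical analysis section says that the effect on primary and secondary outcomes over time "will be computed by using a mixed model linear regression analysis with time, experimental condition and their interaction as independent variables". Before that, for between-group analysis in general, it lists Student's t test or the "Mann-Whitney U test for continuous variables, depending on the normality of the distribution", with normality judged by a Kolmogorov-Smirnov test.

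Table 1 collects the EDE-Q at T0, T1 and T2. App use stops at 12 weeks (T1), and T2 falls 6 months after the start of treatment. The article does not say how time is coded, or which coefficient or contrast decides the primary hypothesis.

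**The concern.** The powered hypothesis concerns one visit. The modelled effect is an interaction that, with three visits, can be summarised in several ways, and these do not all answer the same question. A joint test asks whether the arms diverge anywhere after baseline, so it can be positive because of T2 alone. A linear-time interaction asks about a slope out to T2, some 14 weeks after app use ends, and can miss a real T1 effect that fades. Only a T1 contrast answers the question the trial was sized for. If that contrast is not fixed in advance, the claim on the primary hypothesis could rest on a result that does not bear on it. The stated power would then not describe the test actually used.

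There is also an efficiency point. A model with time, condition and interaction, as written, lets the arms differ freely at T0 although they are randomised. It therefore gives up precision that the baseline EDE-Q, already collected, could supply.

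**Working it through.** **Inputs from the article.** d = 0.40, alpha 0.05, target power 0.80, 100 per arm, 250 recruited, 25% dropout, 1:1 allocation, EDE-Q at T0, T1 and T2, T1 at 12 weeks, T2 at 6 months.

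**Assumptions, not in the article.** Equal SDs at all visits; compound symmetry with between-visit correlation r from 0.3 to 0.7; 6 months taken as 26 weeks; two-sided tests; n = 250 × 0.75 / 2 = 93.75 per arm with data.

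**1. The plan's own figure.** For the independent-samples t-test the noncentrality is d√(n/2). At n = 100 this is 0.40 × √50 = 2.83, giving two-sided power 0.804. So 100 per arm is reproduced as a two-sided test of the T1 difference (a one-sided test would need 78). At n = 93.75 the noncentrality is 0.40 × √46.875 = 2.739 and power is 0.778.

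**2. Joint 2-df interaction, no T1 effect, d = 0.40 at T2.** The contrasts from T0 are (0, 0.40), with covariance (2/n)(1 − r) × [[2, 1], [1, 2]]. The noncentrality is (n/2) × (2/3) × 0.40² / (1 − r) = 46.875 × 0.1067 / (1 − r) = 5 / (1 − r). Against the 2-df chi-square limit of 5.99:

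| r | noncentrality | rejection rate |
|---|---|---|
| 0.3 | 7.14 | 0.665 |
| 0.5 | 10.0 | 0.815 |
| 0.7 | 16.7 | 0.964 |

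**3. Linear time-by-condition interaction.** Weeks 0, 12 and 26, centred, are −12.67, −0.67 and 13.33, with sum of squares 338.67. The standard error of the contrast at r = 0.5 is √(0.5 × 338.67 × 2 / 93.75) = 1.901.

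| Effect at T1, T2 | contrast | noncentrality | power |
|---|---|---|---|
| 0.40, 0.40 (held) | 5.067 | 2.67 | 0.760 |
| 0.40, 0.20 (halved) | 2.400 | 1.26 | 0.243 |
| 0.40, 0 (lost) | −0.267 | −0.14 | 0.052 |

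**4. Contrasts that do target the T1 difference, d = 0.40.** The T1-versus-T0 interaction contrast has the precision of a change score: noncentrality 2.739 / √(2(1 − r)). With baseline adjustment it is 2.739 / √(1 − r²). The unadjusted T1 comparison stays at 0.778 whatever r is.

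| r | T1-versus-T0 contrast | baseline-adjusted T1 difference |
|---|---|---|
| 0.3 | 0.634 | 0.815 |
| 0.4 | 0.701 | 0.844 |
| 0.5 | 0.778 | 0.882 |
| 0.6 | 0.861 | 0.926 |
| 0.7 | 0.940 | 0.968 |

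**5. Sensitivity to n.** With the plan's full 100 per arm the pattern is the same. The 2-df test under step 2 rejects in 0.84 (r = 0.5) to 0.97 (r = 0.7) of trials. The T1-versus-T0 contrast has power 0.66 to 0.95 for r = 0.3 to 0.7. The baseline-adjusted difference has 0.84 at r = 0.3 and 0.90 at r = 0.5.

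**The case against.** Sizing on a t-test and analysing with a mixed model is ordinary practice. A journal article may leave time coding and the reported contrast to an analysis plan that is not shown. With categorical time, the T1-versus-T0 interaction contrast has, under randomisation, the same expectation as the T1 difference, and the same model can also give the T1 difference directly. All of this stands, and it means the planned model is usable. It does not remove the mismatch between the stated target and the stated effect, and the model as written does not use baseline in the more precise way.

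Three stronger readings are tempting and are not supported:

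- *That the plan sets three competing tests.* The Background states a hypothesis, not a test. A T0-to-T1 change difference is simply one contrast of the planned interaction if time is categorical.
- *That the sample size rests on the least efficient option.* The T1 t-test is weaker than a baseline-adjusted analysis. It is stronger than a change score when r is below 0.5, and stronger than a linear slope if the effect fades.
- *That a normality pre-test chooses the primary test.* The t-test or Mann-Whitney rule is written for between-group analysis in general. The intervention effect on the outcomes is assigned to the mixed model. The rule is not expressly excluded for the EDE-Q, so one clarifying sentence is reasonable, but no more.

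It is also fair to say that the scenarios in steps 2 and 3 are illustrations. A full effect appearing only after app use stops has no stated rationale, and the article nowhere says that time is linear or that a joint test decides.

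**Conclusion.** The point holds in a limited form and should be fixed before analysis; it does not undermine the design. The powered quantity is the T1 EDE-Q difference, and the planned interaction is not tied to it. If a joint interaction test were used, it could reject about 82% of the time (about 67% to 96% for r = 0.3 to 0.7) with no T1 effect and d = 0.40 at T2. If time were linear, power for a T1 effect of 0.40 could fall from 76% to 24% or 5% as the effect fades. With the right contrast but no baseline constraint, power is about 63% to 94% over the same range of r, and equals the t-test's 78% only at r = 0.5. Baseline adjustment gives about 84%, 88% and 93% at r = 0.4, 0.5 and 0.6.

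These figures rest on assumed compound symmetry, equal SDs, about 94 per arm and correlations that the article does not give. They do not show that the investigators intend a joint or linear test; they show what is at stake if the contrast is left open.

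**What to change.** Add to the Statistical analysis section:

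- The single primary result is the between-arm difference in EDE-Q at T1, with 95% CI, tested two-sided at 0.05. It comes from the planned mixed model with visit as a categorical factor, visit-by-condition interaction, and baseline EDE-Q as covariate (or arm means constrained equal at T0).
- The T2 contrast from the same model is secondary and addresses maintenance.
- The choice between t-test and Mann-Whitney after the Kolmogorov-Smirnov test does not apply to the primary outcome.

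The cost is wording only: no extra patients or data, and the same SPSS mixed-model procedure. The existing sample size remains a valid basis, because under the working assumptions the baseline-adjusted T1 contrast has at least the power of the t-test used for sizing.
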